#### Process evaluation

##### Working Alliance Inventory – Short (WAI-S; adapted version)

The WAI-short (WAI-S) is a 12-item self-report measure of Working Alliance
[50]. Each item is rated on a 7 point scale, with higher scores indicating higher alliance. The WAI is scored into three subscales measuring Task, Goal and Bond. The Task and Goal scales are intended to measure agreement between the client and therapist with regard to Tasks and Goals of the treatment. The Bond subscale aims to measure the empathic bond between the client and the therapist
[51]. We have adapted the scale by mildly reframing the items to assess internet treatment instead of face-to-face treatment. The WAI will only be administered to participants receiving guidance.

##### Patient satisfaction questionnaire (ZUF-8)

The ZUF-8 is a brief and reliable test-instrument to measure general satisfaction with treatment
[52]. It was originally developed as a modified translation of the 8-item version of the Client Satisfaction Questionnaire
[53] to assess satisfaction with inpatient treatment. It was adapted for this study to assess the satisfaction with the online-based psychological intervention.

#### Other outcomes

##### Questionnaire for the evaluation of psychotherapeutic progress (FEP-2)

The FEP-2 is a measure of therapeutic progress, it can be used for both change and outcome assessment
[54,55]. Forty items measure the dimensions well-being, symptoms, interpersonal relationships, and incongruence with respect to approach and avoidance goals. The instrument has shown to be change sensitive as well as reliable and it is available in the public domain. It represents the phase model of therapeutic change as well as interpersonal and integrative models of psychotherapy
[56].

##### Attitudes toward Psychological Online-Interventions Questionnaire (APOI)

This questionnaire will be developed based on the sample of the EVIDENT study. The development version consists of 35 items that aim at measuring attitudes towards internet-based self-help programs. After conducting exploratory and confirmatory factor analyses at the end of recruitment, the revealed latent structure of multiple factors will be applied to measure changes in participants’ attitudes toward psychological online-interventions on different dimensions. Beyond that, the aim is to identify manifestations on particular attitude dimensions that are obstructive or beneficial for the individual efficacy of internet-based self-help programs.

##### Other questions

Patients are self-reporting a number of demographic variables including sex, marital status, and level of education. They are also asked about the use of other treatments and medication, and about the referral source and internet usage.

### Sample size

The sample size is conservatively based on the expected difference between the intervention and the care-as-usual group on the primary outcome variable (i.e., depressive symptoms measured with the PHQ-9). Although the intervention evaluated in this study also includes guidance for some of the participants, the between-group effect size estimate is based on meta-analytic evidence for the effect observed in unguided psychological interventions (*d* = 0.28)
[22]. Because treatments effects in a sample with mild to moderately depressed participants could even be lower, we conservatively reduced the estimated effect size to *d* = 0.23. Based on this effect size, a power of 0.80, and an alpha level of 0.05, we would need 300 subjects in each condition. Sample size was further estimated based on a drop-out rate of 40%. Drop-out rates in previous studies of the intervention used in this study range from 9%
[33] to 45%
[32], thus this estimate is rather conservative. Previous research shows that drop-out rates are lower in the control group
[14]. Based on this assumption, we will need a total of 1000 subjects. The sample size was calculated using G-Power
[57]. Based on prior experience of users of the intervention, we expect a non-eligible rate of 70% and may therefore have to screen 3333 participants.

### Statistical analysis

A statistical plan will be developed and put down in writing prior to the analysis of the data. The main analyses will be conducted on the intention-to-treat sample. A linear mixed-model repeated measures ANOVA with time (T1-T2-T3-T4) as a within groups factor and treatment condition as a between-groups factor will be used for the main research question. Mixed-model repeated measures ANOVA uses all available data of each subject and does not involve the substitution of missing values. Sensitivity analysis will be conducted to analyze the impact of drop-outs on our results. Secondary analyses of the primary endpoint will include a per-protocol approach. Per-protocol analysis will be based on full data-sets of participants who used at least two sessions of the online-based psychological intervention for a complete duration of at least 60 minutes. The analysis of time to onset of a depressive episode and time to remission of depressive episode will be analyzed using survival analysis techniques. The time to onset of depressive episode will be based on monthly PHQ-9 assessments (these allow the assessment of a probable presence or absence of a depressive episode
[26]) and retrospective assessment of the onset of MDE during the final telephone interview (T4). Significance testing of dichotomous data such as diagnostic status will be conducted with chi-square tests. Calculations of within- and between-groups effect sizes (Cohen’s d) will be based on the pooled standard deviations. Regression analyses will be used to identify predictors of treatment outcome. To analyse the use of health-care resources descriptive methods such as absolute and relative frequency scales, measures of dispersion or measures of central tendency will be used. In order to investigate differences between various patient subgroups appropriate statistical tests will be applied. The assortment of the test will depend on the character of the routine administrative data. All analyses will be performed with SPSS statistics, Excel and Visual Basic for Applications (VBA).

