**Methods/Design:**

This study is a currently recruiting multicentre parallel-groups pragmatic randomized-controlled single-blind trial. A total of 1000 participants with mild to moderate symptoms of depression from various settings including in- and outpatient services will be randomized to an online psychological treatment or care as usual (CAU). We hypothesize that the intervention will be superior to CAU in reducing depressive symptoms assessed with the Personal Health Questionnaire (PHQ-9, primary outcome measure) following the intervention (12 wks) and at follow-up (24 and 48 wks). Further outcome parameters include quality of life, use of health care resources and attitude towards online psychological treatments.

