### Randomization

Subjects will be randomized to two groups (intervention or CAU) after completion of the baseline assessment (online questionnaires and clinical interview via telephone). Stratification at one level will be performed by severity of depressive symptoms. The stratification is designed to ensure equal allocation of participants with mild depressive symptoms (PHQ-9: 5–9) and moderate depressive symptoms (PHQ-9: 10–14) to each of the two study arms. Block randomization with variable block sizes is used. An independent researcher created the allocation schedule with a computerized random number generator; other investigators are blind to this schedule. Allocation is concealed, i.e. patients and researchers have no foreknowledge of, and therefore no control over, the group to which a patient may be allocated. Subjects are informed about the randomization outcome via an email that is automatically sent to participants after the diagnostic interviewer has confirmed that inclusion- and exclusion criteria have been met. The automated email contains a code with which participants randomized to the intervention group can immediately start with the treatment. Diagnostic interviewers will be kept blind to the group assignment of the participants.

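### The 80% power is for one two-group PHQ-9 difference and is not established for the planned repeated-measures ANOVA, which treats baseline as an outcome level

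*Protocol article*

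**What the plan says.** **Sample size.** The calculation rests on the "expected difference between the intervention and the care-as-usual group on the primary outcome variable". The protocol article starts from a meta-analytic d of 0.28 and then says "we conservatively reduced the estimated effect size to *d* = 0.23". With "a power of 0.80, and an alpha level of 0.05, we would need 300 subjects in each condition" and 40% drop-out, it concludes that "we will need a total of 1000 subjects". It names no visit, no correlation between visits and no repeated-measures input.

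**Hypothesis.** The abstract (Methods/Design) expects superiority on the PHQ-9 "following the intervention (12 wks) and at follow-up (24 and 48 wks". It does not rank the three time points.

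**Analysis.** The Statistical analysis section sets out "A linear mixed-model repeated measures ANOVA with time (T1-T2-T3-T4) as a within groups factor", with treatment condition as the between-groups factor, for the main research question. The Assessments section defines T1 as the baseline assessment, made before treatment starts. The text does not say whether the treatment main effect, the time-by-treatment interaction or a contrast at one visit decides. It does say that a statistical plan will be written before the data are analysed.

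**The concern.** The power statement and the planned test concern different quantities. The sample size is for one difference between two arms. A four-level repeated-measures ANOVA offers two default treatment tests, and neither is that difference.

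- **Treatment main effect.** This averages over all four visits. Randomisation makes the expected difference at T1 zero, so a constant later effect is diluted by a quarter.
- **Time-by-treatment interaction.** This has three degrees of freedom and responds to any difference in profile, in either direction. A significant result alone does not show superiority.

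The reader therefore cannot tell what the 80% refers to. With the same data, the trial could succeed or fail according to which term is later read as the answer. Placing T1 among the responses also means that baseline information is not used in the most efficient way.

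**Working it through.** **Inputs from the protocol article:** d = 0.23, alpha 0.05, power 0.80, 300 evaluable per arm, equal arms, drop-out 40% (Sample size; Randomization for equal allocation).

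**Assumed, because the article does not give them:** SD = 1 at every visit, correlation r between visits of 0.3 to 0.7 (compound symmetry unless stated), zero difference at T1, complete data on 300 per arm. Two effect profiles are used: 0.23 at T2, T3 and T4 (constant), and 0.23 at T2 only.

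**1. Reproducing the plan's figure.** A two-sided two-sample comparison needs 297 per arm (normal) or 298 (noncentral t). At 300 per arm the SE of the difference is √(2/300) = 0.0816, the ratio is 0.23/0.0816 = 2.817, and power is Φ(2.817 − 1.960) = 0.804. A one-sided test needs 234 and d = 0.28 needs 201, so neither explains 300. Then 600/(1 − 0.40) = 1000. The sample size is correct for one two-sided, two-group comparison.

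**2. Treatment main effect over T1 to T4.**
- Constant effect: expected difference (0 + 3 × 0.23)/4 = 0.1725, variance (2/300)(1 + 3r)/4.
- r = 0.3: SE 0.0563, ratio 3.07, power 0.87.
- r = 0.5: SE 0.0645, ratio 2.67, power 0.76.
- r = 0.7: SE 0.0719, ratio 2.40, power 0.67.
- T2 only: expected difference 0.23/4 = 0.0575, power 0.18 (r = 0.3) down to 0.13 (r = 0.7).
- AR(1) correlation: constant effect 0.92 to 0.73; T2 only 0.20 to 0.14.

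**3. Time-by-treatment test, 3 df.** The noncentrality is (300/2) × Σ(δₜ − mean δ)²/(1 − r). For the constant profile the sum is 0.1725² + 3 × 0.0575² = 0.0397, so the noncentrality is 5.95/(1 − r). Power of 80% needs about 10.9.
- Compound symmetry: noncentrality 8.5, 11.9 and 19.8 at r = 0.3, 0.5 and 0.7; power 0.68, 0.84 and 0.97. The T2-only profile has the same sum of squares and the same power.
- AR(1), constant effect: 0.58, 0.70 and 0.89.
- Direction: take differences of −0.15, 0 and +0.15 at T2, T3 and T4, so that the average follow-up difference is zero. The noncentrality is 150 × 0.045/(1 − r), which is 9.6 at r = 0.3 and 13.5 at r = 0.5, and the test rejects about 74% and 88% of the time.

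**4. Single-visit contrasts at T2, d = 0.23 at T2.**

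| Contrast | Variance | r = 0.3 | r = 0.5 | r = 0.7 |
|---|---|---|---|---|
| Difference at T2, unadjusted | 2/300 | 0.80 | 0.80 | 0.80 |
| Change from T1 to T2 | (2/300) × 2(1 − r) | 0.66 | 0.80 | 0.95 |
| T2 adjusted for T1 | (2/300)(1 − r²) | 0.84 | 0.90 | 0.98 |

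**5. Sensitivity to the SD assumption.** Entry is restricted to PHQ-9 scores of 5 to 14, which may make the baseline SD smaller than later ones. With a baseline SD of 0.6 times the follow-up SD, the change contrast has variance (2/300)(1 + 0.36 − 1.2r), giving 0.80 at r = 0.3 and 0.90 at r = 0.5. The adjusted contrast stays at 0.84 and 0.90. Over the same r range the default terms also gain for a constant effect under compound symmetry: main effect 0.92 to 0.76, interaction 0.92 to 0.99. The T2-only main effect stays low, at 0.20 to 0.14.

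**The case against.** The strongest reply is that the article is condensed and promises a written statistical plan. Which term decides, and how the visits are ordered, are commonly left to such a plan. That stands: the missing name of a contrast would not be a finding by itself. What the article does fix is a model with baseline among the responses, next to a power figure for a different quantity.

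A reader might infer that the planned test lacks 80% power. The calculations do not support this. Power exceeds 80% in many plausible settings, and the documents give neither correlations nor an effect profile. The figures also use completers only; a mixed model that uses partial records would do somewhat better.

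A reader might also infer that the model cannot test the stated hypothesis. It can. The differences at 12, 24 and 48 weeks can be estimated from its time-by-treatment terms, and the unadjusted T2 difference keeps the planned 80%. The text simply does not say that such a contrast decides.

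Finally, a reader might infer an inflated type I error from the three time points. That would require a rule under which any one significant visit counts as success, and no section states one.

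**Conclusion.** The point holds as a mismatch between the power statement and the planned analysis, not as proof of an underpowered trial. The sample size arithmetic is right for one two-group comparison. For the ANOVA as written, 80% is not established. With 300 completers per arm, equal SDs and r from 0.3 to 0.7, a constant effect gives the main effect 67-87% (compound symmetry; 73-92% under AR(1)) and the 3-df test 58-97% across both structures. An effect confined to T2 leaves the main effect at no more than about 20%. All of these ranges depend on the assumed correlations, SDs and effect profiles.

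The case for change is that a better analysis costs almost nothing. With equal SDs, moving T1 to the covariate side raises a T2 contrast from 66-80% (change from baseline) to 84-90% for r of 0.3 to 0.5. The gain over the change contrast shrinks if the baseline SD is much smaller than the follow-up SD, but the adjusted contrast was never the weaker of the two in these calculations.

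**What to change.** In the protocol and the statistical plan, before unblinding:

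1. Use T1 PHQ-9 as a covariate and keep only T2, T3 and T4 as responses in the mixed model.
2. Name one model-based between-arm contrast as decisive, for example the difference at T2, the end of treatment.
3. Make the other visits secondary, or test them in a fixed sequence at 0.05 after the decisive contrast.
4. State that neither the treatment main effect nor the omnibus interaction is the decision test.
5. State that the 80% refers to the named contrast with 600 evaluable participants.

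No new data and no change in sample size are needed. The cost is that claims at the later visits become secondary or conditional on the first test. T2 is one defensible choice of visit among several; what matters is that one is fixed in advance.

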## Methods

### Study design

This study is a parallel-groups pragmatic randomized controlled single-blind trial. Subjects will be randomized into two groups: (1) Care-as-usual (CAU) or (2) CAU plus online-based psychological treatment. Participants in the intervention group with mild depressive symptoms will receive access to an unguided online psychological treatment, whereas those with moderate symptoms will receive the same treatment plus e-mail support (guided self-help). The study is being conducted in compliance with the Declaration of Helsinki
[27]. It has been approved by the Ethics Committee of the German Psychological Association (DGPs, reference number SM 04_2012). All participants receive written information about the aim of the study, benefits and risks of participation and the study procedure. They are informed that they can withdraw at any time without having to disclose reasons. Informed consent will be obtained online prior to the baseline assessment. A written study protocol has been developed. Results will be reported in accordance with the CONSORT guidelines
[28]. The study design is shown in Figure 
1.

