### Inclusion and exclusion criteria

The main inclusion criterion for this study is the presence of mild to moderate depressive symptoms, operationalized as a score between 5 and 14 on the PHQ-9
[26]. Participants are required to be between 18and 65 years of age, have internet-access and be able to communicate in German. The main exclusion criteria are acute suicidality and a lifetime diagnosis of bipolar disorder or schizophrenia. The presence of these diagnoses will be assessed using the Mini International Neuropsychiatric Interview [MINI: 29] via telephone. Acute suicidality will be assessed clinically based on a structured assessment of current suicidal ideation and past suicide attempts
[29-31]. Participants who do not meet our inclusion criteria due to severity of illness are encouraged to seek professional help.

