### Assessments

There will be a total of four assessments. The first assessment (baseline, T1) will be before the start of the intervention. Other assessments will take place at 3 months (directly following the intervention, T2), 6 months (T3), and 12 months (T4) after baseline (see Table 
1). All self-report assessments will be performed via online questionnaires conducted via an online-survey program (http://www.unipark.de). At T1, T2 and T3 an additional diagnostic interview will be conducted via telephone in which the Mini International Neuropsychiatric Interview (MINI)
[29], the Hamilton Depression Rating Scale (HDRS)
[30] and the Quick Inventory of Depressive Symptomatology (QIDS)
[34] are administered. All clinical interviews will be conducted by certified raters. Raters are advanced university students or graduates majoring in psychology or medicine. They will all have completed training, including at least one audiotaped interview and the observation of ratings by experienced raters. In addition to the four outcome assessments, the primary outcome measure (PHQ-9) will be administered weekly in the intervention group via the online intervention and monthly for both groups during the follow-up period via a link to an online-survey that is sent via email automatically.

**Table 1 T1:** Study assessments and assessment time points

	**Online self-assessment**									**Clinician assessment via telephone**		
	**PHQ-9**	**WSQ**	**D-CAT**	**SF-12**	**APOI**	**FEP-2**	**WAI-S**^**1,2**^	**ZUF-8**^**1**^	**Ressource use**	**HRSD**	**QIDS**	**MINI**
T1 baseline	X	X	X	X	X	X			X	X	X	X
Post randomisation	X											
T2 post-intervention	X	X	X	X	X	X	X	X	X	X	X	X
Monthly	X											
T3 three month follow-up	X	X	X	X	X	X			X			
Monthly	X											
T4 nine month follow-up	X	X	X	X		X			X	X	X	X

^1^Only patients randomized to the online psychological intervention.

^2^Only patients with moderate symptoms (PHQ-9 10–14) who also get e-mail-support.

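### The primary model treats baseline PHQ-9 as an outcome level and uses neither it nor the randomisation stratum for adjustment, which can cost precision but does not bias the result

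*Protocol article*

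**What the plan says.** In the protocol article, the Statistical analysis section gives the main model by its factors: "A linear mixed-model repeated measures ANOVA with time (T1-T2-T3-T4) as a within groups factor and treatment condition as a between-groups factor". The same sentence ties this model to the primary comparison: "treatment condition as a between-groups factor will be used for the main research question". The Assessments section makes clear that T1 precedes treatment: "The first assessment (baseline, T1) will be before the start of the intervention". Baseline PHQ-9 is thus one of the four outcome levels. No baseline covariate, stratum term or equal-baseline constraint is named.

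The Randomization section states: "Stratification at one level will be performed by severity of depressive symptoms". Its aim is "equal allocation of participants with mild depressive symptoms (PHQ-9: 5–9) and moderate depressive symptoms (PHQ-9: 10–14) to each of the two study arms". The stratum is therefore the baseline value of the primary outcome cut in two. The Study design section uses the same cut to decide whether the online treatment comes with e-mail support.

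Baseline severity reappears only in the Discussion, as a subgroup factor. The Statistical analysis section plans regression only to look for predictors of outcome. It also announces a written statistical plan, to be completed before the data are analysed; that plan is not shown.

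**The concern.** Baseline PHQ-9 and the severity stratum are known for every participant before randomisation, and both are likely to predict later PHQ-9. A model that puts T1 among the responses and leaves the arm means at T1 free estimates the effect at T2 as the arm difference in change from T1. That contrast carries the noise of the baseline measurement as well as the follow-up measurement. Conditioning on baseline removes the part of the follow-up variance that baseline explains and does not add the baseline noise back.

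What is at stake is precision. The trial is planned around a small effect ("we conservatively reduced the estimated effect size to *d* = 0.23") and expects 40% drop-out, so power given away in the analysis is expensive to recover by recruiting.

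**Working it through.** **Plan's own figure.** Inputs from the Sample size section: d = 0.23, power 0.80, alpha 0.05 (taken as two-sided).

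- n per arm = 2 × (1.960 + 0.842)² / 0.23² = 297 (298 with the t distribution). The article says 300.
- Allowing for 40% drop-out: 600 / 0.60 = 1000, as stated.
- Power at 300 per arm is 0.804.

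The stated figures reproduce as an unadjusted two-group comparison.

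**Contrast variances.** Let ρ be the correlation between T1 and follow-up PHQ-9, and k the baseline SD divided by the follow-up SD. The article gives neither, so both are assumed and shown as ranges. In units of the follow-up variance, with complete data and 300 per arm:

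- change contrast (T1 means free): k² + 1 − 2ρk
- baseline-adjusted contrast: 1 − ρ²
- difference: k² + 1 − 2ρk − (1 − ρ²) = (k − ρ)²

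The adjusted variance is never larger, and the two are equal only when ρ = k.

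**Power.** For a contrast with variance v, power = Φ(0.23 × √(300/2) / √v − 1.96), with d standardised on the follow-up SD. Example for k = 1, ρ = 0.3: v = 1 + 1 − 0.6 = 1.40 gives 2.817/1.183 − 1.96 = 0.42, power 0.663. Adjusted, v = 0.91 gives 2.817/0.954 − 1.96 = 0.99, power 0.840.

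| k | ρ | Variance, change | Variance, adjusted | Ratio | Power, change | Power, adjusted | Loss (points) |
|---|---|---|---|---|---|---|---|
| 1.0 | 0.3 | 1.40 | 0.91 | 1.54 | 0.663 | 0.840 | 17.7 |
| 1.0 | 0.4 | 1.20 | 0.84 | 1.43 | 0.730 | 0.867 | 13.7 |
| 1.0 | 0.5 | 1.00 | 0.75 | 1.33 | 0.804 | 0.902 | 9.8 |
| 0.8 | 0.3 | 1.16 | 0.91 | 1.27 | 0.744 | 0.840 | 9.6 |
| 0.8 | 0.5 | 0.84 | 0.75 | 1.12 | 0.867 | 0.902 | 3.5 |
| 0.6 | 0.3 | 1.00 | 0.91 | 1.10 | 0.804 | 0.840 | 3.6 |
| 0.6 | 0.4 | 0.88 | 0.84 | 1.05 | 0.851 | 0.867 | 1.6 |
| 0.6 | 0.5 | 0.76 | 0.75 | 1.01 | 0.898 | 0.902 | 0.4 |

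**Which k is plausible.** Entry requires depressive symptoms "operationalized as a score between 5 and 14 on the PHQ-9", while the scale runs from 0 to 27, so k below 1 is likely. If scores were spread evenly over 5 to 14, the baseline SD would be 2.87, and k = 0.6 would correspond to a follow-up SD of 2.87/0.6 = 4.8. This is an illustration; the article reports no SD.

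**When the planned power is met.** The change contrast has a variance of at most 1, the value behind the sample size, only if k ≤ 2ρ. The adjusted contrast has a variance of at most 1 whatever k is.

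**What the stratum contributes.** Under the same even spread, the stratum correlates 0.87 with baseline PHQ-9. Adding stratum-by-time to the change model gives a variance of (k − ρ)²(1 − 0.87²) + 1 − ρ². For k = 1, ρ = 0.5 this is 0.81, against 1.00 without it and 0.75 with continuous baseline. The stratum thus recovers much of the loss when continuous baseline is absent, and little remains for it once continuous baseline is in the model.

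**The case against.** The strongest reply is that the article condenses the analysis and announces a fuller plan. Covariates, covariance structure, baseline constraints and the contrast to be tested are commonly settled there. The text does not say that time and treatment are the only terms, and a mixed model with T1 as a response and a common baseline mean would be about as efficient as baseline adjustment.

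Part of this stands. T1 as a response is not a fault in itself; the loss arises only if the T1 means are left free, and the article does not say whether they are. But the article does not leave the model open. It lists the factors and places T1 among the outcome levels, so a plan that conditioned on T1 would change the stated model.

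The reply is also right that several stronger readings go too far:

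- *The trial is underpowered.* A reader might infer this from the power of 0.66. That figure needs k = 1 and ρ = 0.3. At k = 0.6 and ρ of 0.3 or more, the change contrast still reaches the planned 0.80.
- *The gain is worth 30 to 100 completers per arm.* A reader might compute 300/(1 − ρ²) = 330 to 400. That compares adjustment with an analysis of T2 alone that ignores T1, not with the time-by-treatment contrast of the stated model.
- *The restricted T1 range breaks a common-variance model.* The article states no covariance structure, so this cannot be said of it.
- *Adding the stratum alone would solve the problem.* A stratum main effect does not sharpen a time-by-treatment contrast, because stable differences between persons already cancel in it. Stratum-by-time or continuous baseline is needed.

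**Conclusion.** The point holds as a matter of efficiency. As stated, the primary model uses neither baseline PHQ-9 nor the randomisation stratum for adjustment. With free T1 means its time-by-treatment contrast is never more precise than a baseline-adjusted one. For ρ of 0.3 to 0.5, the loss is about 0 to 4 power points at k = 0.6 and about 10 to 18 points at k = 1. The restricted entry range favours values nearer the lower end, but the article cannot settle it. The figures assume complete data on 300 per arm and a test of the T1-to-T2 contrast, which the article does not name explicitly.

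A reader might go further and infer a biased estimate, invalid inference or a faulty sample size. The article supports none of these: randomisation protects the comparison, leaving out a stratification factor makes standard errors conservative if anything, and the 300 per arm and 1000 in total reproduce. The change is an improvement worth making because it is nearly free, not the repair of an invalid analysis.

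**What to change.** State the primary model in the statistical plan, before the data are analysed, in one of two forms:

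1. PHQ-9 at T2, T3 and T4 as responses, with fixed effects for treatment, time, treatment-by-time, continuous T1 PHQ-9, T1 PHQ-9-by-time and the severity stratum, and an unstructured covariance.
2. PHQ-9 at T1 to T4 as responses, with the T1 mean constrained to be equal between arms, stratum-by-time added, and an unstructured covariance. This form also keeps participants who have only a T1 score in the model, in line with the intention-to-treat sample.

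In either form, name the treatment contrast to be tested. The stratum adds little precision beyond continuous baseline; it is included so that the analysis reflects the randomisation.

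The cost is a sentence or two in the plan. T1 PHQ-9 and the stratum are recorded before randomisation, so no data collection, visit or sample size changes.

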### Outcome measurements

#### Primary outcome

##### Depressive symptoms

Symptoms of depression will be measured with the *Patient Health Questionnaire (PHQ-9)*[26]. The PHQ-9 is a self-administered version of the PRIME-MD diagnostic instrument for common mental disorders
[2,26]. The PHQ-9 is the depression module, which scores at each of the 9 DSM-IV criteria on a 4-point Likert-scale from “0” (not at all) to “3” (nearly every day)
[2]. The PHQ-9 score can thus range from 0 to 27. The PHQ-9 has been shown to be sensitive to change
[35-38]. It can also be used as a diagnostic algorithm to make a probable diagnosis of a depressive episode
[26]. The primary outcome measure (PHQ-9) will be administered once per month during the follow-up period (after the initial 12 weeks) to allow for a relatively fine-grained analysis of symptom fluctuations over time.

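### The main model omits the monthly follow-up PHQ-9 scores, so the 6- and 12-month contrasts can be biased if drop-out follows recent scores differently by arm

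*Protocol article*

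**What the plan says.** The Assessments section sets four main assessments: baseline (T1), 3 months (T2), 6 months (T3) and 12 months (T4). In addition, the PHQ-9 is given "monthly for both groups during the follow-up period via a link to an online-survey that is sent via email automatically". Table 1 shows the same, with a monthly PHQ-9 row between T2 and T3 and another between T3 and T4. The Primary outcome section gives the reason: the PHQ-9 "will be administered once per month during the follow-up period (after the initial 12 weeks) to allow for a relatively fine-grained analysis" of how symptoms fluctuate.

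The Statistical analysis section specifies "A linear mixed-model repeated measures ANOVA with time (T1-T2-T3-T4) as a within groups factor and treatment condition as a between-groups factor" for the main research question and adds: "Mixed-model repeated measures ANOVA uses all available data of each subject and does not involve the substitution of missing values". It continues: "Sensitivity analysis will be conducted to analyze the impact of drop-outs on our results". The method of that sensitivity analysis is not given, and a written statistical plan is to follow before the data are analysed. The section names one use of the monthly scores: "The time to onset of depressive episode will be based on monthly PHQ-9 assessments", together with the retrospective interview at T4.

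The abstract's superiority hypothesis covers 12, 24 and 48 weeks. The Sample size section assumes 40% drop-out and notes that drop-out has been lower in control groups.

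**The concern.** A likelihood-based mixed model needs no imputation as long as the data in the model account for who goes missing. Between T3 and T4 this model contains nothing for six months, although the same instrument is collected by the same online route in both arms. Someone who answers through month 10 and then stops enters the model as last seen at month 6.

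If people leave after a good or a bad month, the T1-T4 scores alone may not explain the missing T4 values. If that pattern also differs between arms, the error does not cancel in the treatment contrast. Two of the three time points in the hypothesis, 24 and 48 weeks, are exposed, and the planned effect is small (d = 0.23). The direction cannot be known in advance: the bias can inflate or shrink the effect.

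**Working it through.** **1. Scores left out.** With T2, T3 and T4 at months 3, 6 and 12, the monthly surveys fall at about months 4 and 5, and 7, 8, 9, 10 and 11: 2 + 5 = 7 per person. Both arms are therefore scheduled for 4 + 7 = 11 PHQ-9 scores, of which the main model uses 4.

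**2. The plan's own figure.** n per arm = 2 × (1.960 + 0.842)² / 0.23² = 297 (298 with the t distribution), against 300 stated. Then 300 / (1 − 0.40) = 500 per arm, 1000 in total. The sample size reproduces and is not in dispute.

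**3. First simulation** (assumptions not in the protocol).
- 500 per arm, 1,500 runs per scenario, true T4 difference 1.0 point, SD 4.5 (3.0 at baseline).
- Covariance: shared part 0.45, autoregressive part 0.35 with 0.8 per month, noise 0.20. The T3-T4 correlation is 0.45 + 0.35 × 0.8⁶ = 0.54, and month 11 to T4 is 0.45 + 0.35 × 0.8 = 0.73.
- Monotone drop-out of about 40%, with the hazard depending on the last score. About 14% of each arm stop after month 7 but before T4.

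| Log-hazard ratio per SD, control / intervention | T4 bias, four visits (points) |
|---|---|
| 0 / 0.3 | −0.08 |
| 0 / 0.6 | −0.18 |
| −0.3 / 0.3 | −0.16 |
| 0 / −0.3 | +0.08 |

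These are 8 to 18% of the true effect, or 0.08/4.5 = 0.018 to 0.18/4.5 = 0.040 SD. The T3 bias was 0.02 to 0.06 points. With the monthly scores added, the T4 bias lay between −0.01 and +0.01. Under random drop-out the T4 variance was 3.5% larger with four visits (ratio 1.035).

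**4. Second simulation**, built separately, with unit SD.
- 300,000 participants per scenario and a true effect of −0.23 at every visit after baseline.
- 15% of controls and 25% of the intervention arm lost at random before T2, then a monthly hazard of about 3%. In total 39 to 44% are missing at T4.
- Four correlation structures: stable part 0.1 to 0.5, serial correlation 0.7 to 0.9 per month. The table gives ranges over the four.

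| Dependence of drop-out on last score (log-odds per SD) | T3, four visits | T4, four visits | T4 with monthly scores |
|---|---|---|---|
| None | −0.226 to −0.235 | −0.226 to −0.231 | −0.227 to −0.230 |
| 0.5, both arms | −0.226 to −0.235 | −0.220 to −0.236 | −0.223 to −0.238 |
| 1, both arms | −0.225 to −0.234 | −0.212 to −0.229 | −0.225 to −0.241 |
| 0.5, intervention only | −0.231 to −0.242 | −0.245 to −0.265 | −0.224 to −0.239 |
| 1, intervention only | −0.236 to −0.251 | −0.266 to −0.295 | −0.223 to −0.234 |
| ±0.5, opposite by arm | −0.239 to −0.252 | −0.263 to −0.294 | −0.223 to −0.232 |
| ±1, opposite by arm | −0.260 to −0.280 | −0.320 to −0.375 | −0.222 to −0.233 |

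With about 90,000 per arm left at T4, the simulation error is roughly √(2/90,000) = 0.005, so departures of about 0.01 are noise.

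T4 bias as a share of 0.23:
- 0.5, intervention only: 0.015/0.23 = 7% to 0.035/0.23 = 15%.
- 1, intervention only, or ±0.5: 0.033/0.23 = 14% to 0.065/0.23 = 28%.
- ±1: 0.090/0.23 = 39% to 0.145/0.23 = 63%.
- Equal dependence: at most about 0.02 SD (0.230 − 0.212 = 0.018).

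The T2 estimate stayed near −0.23 throughout. When people who leave do not return, scores after T2 carry no information for the T2 contrast, so the two models agree there.

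**5. Scale.** With 300 completers per arm, the standard error at T4 is about √(2/300) = 0.082 SD. A bias of 0.015 to 0.040 SD is 0.2 to 0.5 of it.

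**6. Who can be helped.** In the second simulation 20% are gone before T2, about half of the 39 to 44% missing at T4. They have no monthly score.

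**The case against.** The strongest reply is that the quoted sentence describes a general property of mixed models: participants with incomplete visits stay in and nothing is imputed. It directly follows a model defined on T1-T4 and is true of those visits. That stands. A reader might infer that the article makes a false statement about its analysis, but the text supports only that the wording is loose.

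Modelling the visits named in the hypothesis is also ordinary practice, and the monthly scores are not idle: the article assigns them to symptom fluctuation and to time to onset of an episode. A drop-out sensitivity analysis is promised, and the statistical plan, which is not shown, may use the monthly scores there. All of this stands and lowers the weight of the point. It does not change the main model, whose time points the article fixes itself.

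The size rests on assumptions. The article says only that drop-out tends to be lower in controls; it does not say that leaving depends on scores, still less differently by arm. Nor does it say when the 40% leave. Both simulations used monotone drop-out driven by the last observed score, which suits the remedy. They did not test skipped surveys or a misspecified structured covariance. These limits stand too.

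**Conclusion.** The point holds in a conditional and modest form. Primary-outcome scores that both arms provide are left out of the main model, and this can bias T3 and especially T4 if drop-out after T2 depends on recent monthly scores differently by arm. Under moderate assumed dependence the T4 bias is about 0.02 to 0.04 SD, or 7 to 18% of the planned effect. It is larger under stronger or opposite dependence, and near zero if drop-out is random or the dependence is equal in both arms. T2 and the total of 1000 are unaffected.

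Two stronger readings are not supported. One is that the 6- and 12-month results will be biased: nothing in the article establishes the drop-out pattern this requires. The other is that the monthly scores would remove drop-out bias. They reduce it only for people who answer some surveys after T2 and then miss T3 or T4. They do nothing for people lost before T2, or where leaving depends on scores never observed.

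**What to change.** In the Statistical analysis section, fit the mixed model to T1, T2, the monthly follow-up scores, T3 and T4, with categorical time by arm. Use an unstructured covariance where it converges and a pre-specified structured one otherwise. Report treatment contrasts at T2, T3 and T4 only. Make this the main model, with the four-visit model as sensitivity analysis. At minimum, name it as the drop-out sensitivity analysis already promised.

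Leave out the weekly in-programme scores, which the Assessments section describes for the intervention arm only. Reword the sentence so that it claims *all available data at the modelled visits*.

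The cost is wording and a larger covariance: 11 × 12 / 2 = 66 parameters when unstructured, against 4 × 5 / 2 = 10 for four visits, so a structured form may be needed. No new data, visits or participants are required.
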